### Data Collection and Management

Data will be collected online at baseline, and at 1, 2, and 3 months postbaseline. Participants will be invited to complete follow-up assessments online via a link sent by email and/or text message in the first instance and followed up by telephone thereafter. For analysis, participants will be assigned a unique patient identifier. De-identified data on rate of referral and frequency, type, and duration of health service contact resulting from use of the online intervention will be provided by the health service using the unique patient identifier allocated to each participant. Data collected online will be de-identified and uploaded automatically to a secure server managed by the primary sponsor (South Australian Health and Medical Research Institute) in accordance with strict research governance protocols [35]. Contact details are necessary for the successful operation of the online intervention but will not be stored with data collected for research purposes. Access to data will be limited to research staff named on the ethics protocol.

### Statistical Analyses and End Points

An intention-to-treat analysis will compare the primary and secondary outcomes for the intervention versus placebo conditions at 1, 2, and 3 months from baseline. Main effects will be evaluated using a mixed effect model that accounts for site-specific clustering effects.

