**Methods:**

Participants will be Aboriginal and Torres Strait Islander people aged 16 years and over who have used methamphetamine at least weekly for the previous 3 months. They will be recruited online and via health services. During the intervention phase, participants will have access to the online intervention for 6 weeks with optional telephone or face-to-face support provided by participating health services. The primary outcome measure will be the number of days the participant used methamphetamine over the past 4 weeks compared to wait-list controls, assessed at baseline, 1, 2, and 3 months. Secondary outcomes will include help-seeking, readiness to change, severity of dependence, and psychological distress. Any important changes to the protocol will be agreed upon by the trial management committee and communicated to all relevant parties, including trial site representatives and the trial registry.

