### Objective

Our primary hypothesis is that participants who complete the We Can Do This online intervention will have significantly reduced days of methamphetamine use in the last 4 weeks at 1, 2, and 3 months from baseline compared with wait-listed participants with access to treatment as usual. Our secondary hypothesis is that the program will increase intended and actual help-seeking, including attendance at participating health services.

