### Randomization

The randomization scheme will be developed by a statistician who is not involved with study participants. Subjects will be randomly allocated to the online intervention or the wait list with 1:1 ratio. Random numbers will be generated using the statistical software Stata 14.0 or higher version (StataCorp LLC).

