### Sample Size and Power

Based on our previous research, we expect a baseline mean of 16 days methamphetamine use in the past 4 weeks [33]. We aim to detect a reduction to a mean of 8 use days in the past 4 weeks, as this will have a significant clinical impact in terms of reducing the risk of psychotic symptoms and violence (reduction from odds of 10-11 to 2-3) [33,34]. To detect this difference at each of the follow-up points with 90% power at a *P*<.01 level, we will require a sample of 100 participants per group. Based on our previous research, with assertive follow-up (ie, by phone as well as by email/text) we expect up to 30% attrition at follow-up, meaning that we will need to recruit 144 participants into each condition (intervention and treatment as usual) or a total of 288 participants. Treatment sites will be ACCHSs and other relevant services with Aboriginal clients.

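### The stated model evaluates main effects with site clustering, but the hypothesis and power statement need arm contrasts at 1, 2 and 3 months; baseline use days are given no role

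*Protocol article*

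**What the plan says.** The analysis section (Protocol article, Statistical Analyses and End Points) has two sentences. The first fixes the comparison: "An intention-to-treat analysis will compare the primary and secondary outcomes for the intervention versus placebo conditions at 1, 2, and 3 months from baseline". The second fixes the model: "Main effects will be evaluated using a mixed effect model that accounts for site-specific clustering effects".

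The Objective is visit-specific. It predicts "significantly reduced days of methamphetamine use in the last 4 weeks at 1, 2, and 3 months from baseline". Sample Size and Power asks for 90% power at P<.01 separately at each follow-up.

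The outcome is measured repeatedly: "Data will be collected online at baseline, and at 1, 2, and 3 months postbaseline". The Methods paragraph of the Abstract says that the primary measure is "assessed at baseline, 1, 2, and 3 months". Under Participant Eligibility, Recruitment, and Consent, the baseline assessment comes before randomisation. Allocation is by individual: "Subjects will be randomly allocated to the online intervention or the wait list with 1:1 ratio".

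No arm-by-time term, participant-level term or baseline covariate is mentioned. None is ruled out either.

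**The concern.** The effect named in the model sentence is not the effect that the rest of the article sets out to test. In one longitudinal model, the group main effect is a single number averaged over visits. It answers whether the arms differ on average over follow-up, not whether they differ at 1, at 2 and at 3 months.

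The difference could matter here. The Abstract gives participants access to the intervention for 6 weeks, and the outcome looks back 4 weeks. The month 1 window lies inside the access period, the month 2 window straddles its end, and the month 3 window lies after it. An effect that changes across visits is therefore plausible, and averaging would hide the change.

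Two further matters depend on how the sentence is carried out. It names one source of dependence, site. Because individuals are randomised, both arms largely share site. The dependence that matters more for error control is between repeated counts from the same person. And a baseline count that is already collected could sharpen every contrast at no cost, yet the model sentence gives it no place.

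**Working it through.** **The plan's own figure.** The article gives no number for the analysis model. The nearest is 100 participants per group. It cannot be reproduced because no standard deviation is stated, and nothing below depends on it except as the group size in a simulation. The attrition step, 100/0.7 = 142.9, rounds up to 143 against the stated 144.

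**1. Main effect against visit contrasts.** Let d1, d2 and d3 be the arm differences at 1, 2 and 3 months. With equal weight per visit, the group main effect is (d1 + d2 + d3)/3. It equals the visit contrasts only if d1 = d2 = d3. Otherwise the three values cannot be recovered from it. They need an arm-by-time term or a separate model per visit.

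**2. Timing.** Taking a month as 52/12 = 4.33 weeks, the visits fall at weeks 4.3, 8.7 and 13. The 4-week windows are about weeks 0.3 to 4.3, 4.7 to 8.7 and 9 to 13, against access to week 6.

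**3. Error rate if the follow-ups are stacked with a site effect only.** Assume exchangeable correlation rho between the three counts from one person. The documents give no value, so a range is shown.

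- True variance of a person's mean over three visits: s²(1 + 2·rho)/3.
- Variance if the rows are treated as independent: s²/3.
- True SE / model SE = sqrt(1 + 2·rho).
- Actual two-sided type I error = 2·(1 − Φ(z / sqrt(1 + 2·rho))), with z = 2.576 for 1% and 1.960 for 5%.

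| rho (assumed) | SE ratio | Nominal 1% becomes | Nominal 5% becomes |
|---|---|---|---|
| 0.3 | 1.265 | 4.2% | 12.1% |
| 0.5 | 1.414 | 6.9% | 16.6% |
| 0.7 | 1.549 | 9.6% | 20.6% |

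The 1% column is the relevant one, because P<.01 is the only level that the article states. It does not say whether that is one- or two-sided; two-sided is taken here.

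**4. Simulation check.** Settings: 4,000 runs, 100 per arm, normal outcomes, no missing data, 10 sites and site intraclass correlation 0.02 (both assumed), site fitted as fixed effects. At nominal 1%:

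| rho | Three visits stacked, site only | One visit (month 3), site only |
|---|---|---|
| 0.3 | 4.1% | 1.0% |
| 0.5 | 7.2% | 0.9% |
| 0.7 | 10.2% | 1.2% |

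The stacked results agree with the formula. A model for one visit has one row per person, and each such test keeps its nominal level.

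**5. Baseline as covariate.** With correlation r between baseline and one follow-up, linear adjustment multiplies the variance of the arm contrast at that visit by 1 − r². The documents do not give r.

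| r (assumed) | Variance factor | Per group, adjusted, for the precision of 100 unadjusted |
|---|---|---|
| 0.3 | 0.91 | 91 |
| 0.5 | 0.75 | 75 |
| 0.7 | 0.51 | 51 |

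**The case against.** This is a condensed journal article. Covariance structure, interaction terms and covariates are commonly left to a full protocol or SAP, and neither is shown. The text does not say that site is the only random effect, that visits are pooled as independent rows, or that baseline days are left out. Comparing the arms at three visits can be read as three separate models, for which the error rate is nominal. Main effects may also be loose wording for the treatment effects.

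Most of this stands, and it rules out several stronger readings. A reader might infer that the plan ignores repeated measures and so will inflate its false-positive rate. The documents do not support that, since it needs one particular implementation that they do not describe. A reader might infer that baseline is discarded and the estimate biased. Exclusion is not stated, and leaving baseline out of a randomised comparison costs precision without causing bias. From the Abstract's list of assessment times, a reader might infer that baseline enters as a response and dilutes the main effect. That list says when the measure is taken, and the analysis section names only the three follow-ups as comparison points.

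The objection does not remove the mismatch in the text as published. The article chose to name the effect, and the term it chose does not yield the contrasts that its own Objective, power statement and first analysis sentence require.

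**Conclusion.** The point holds in a limited form. The model sentence should be changed because a group main effect does not deliver the comparisons at 1, 2 and 3 months that the article hypothesises and powers, and because it gives no role to a pre-randomisation count that is already collected.

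The error-rate consequence is conditional. It is about 4% to 10% at nominal 1% for assumed rho of 0.3 to 0.7 if follow-ups are stacked without a participant term, and nil for separate visit models. The published text does not say which applies. The precision on offer is a 9% to 49% cut in variance at a visit for assumed r of 0.3 to 0.7. Both ranges rest on assumed correlations, normal-theory formulas and, for the first, equal correlation between visits.

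**What to change.** Replace the main-effects sentence with a statement that the treatment effects are the arm contrasts at 1, 2 and 3 months. They should come from a mixed model with the three follow-up counts as responses; fixed effects for arm, time, arm-by-time and baseline use days; site as a fixed or random effect; and a participant random effect or an unstructured within-person covariance. The contrasts should cover all three visits, because the article names no single primary one. If an average over follow-up is what the investigators want, the Objective and the power statement should say so instead.

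If a full protocol or SAP already specifies this, only the article's wording needs to be aligned with it. The cost is about two sentences, with no change to data collection or trial conduct. The change should be made before outcomes are analysed by arm.

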### Safety and Security

The safety and security of participants is of paramount concern at all stages of the research process. To address issues of safety, the participant information sheet provided to participants will include emergency numbers of appropriate providers in the local area and the contact numbers of the relevant researchers. These will also be included online at the end of baseline and follow-up assessments. Adverse events or unintended effects of the trial reported by participants or clinicians involved in the trial will be assessed by the trial management committee and reported to the ethics committees and other parties as required.

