## Methods

### Trial Design

A 2-group randomized controlled trial will be used. The intervention group will receive the We Can Do This online intervention with the option of telephone or face-to-face support provided by their local ACCHS staff. The wait-list control group will undertake the same assessments as the intervention group and have access to treatment as usual at the participating health services until the 3-month control period is complete, at which point they will receive access to the online intervention. They will receive reminders to log in but no further research assessments. Nonidentifiable use data will continue to be monitored. Treatment as usual will involve referral to online harm minimization information and access to alcohol and other drug counseling at the participating health service. The flow of participants through the trial is shown in Figure 1.

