**Figure 1 figure1:**
[figure not shown]
Flow of participants through the We Can Do This trial. AOD: alcohol and other drugs; MH: mental health.

Participants will have the option of receiving health practitioner support via weekly phone calls from trained staff at the participating health service in their geographical area. If this option is selected, participant contact details will be forwarded to the relevant health service, and they will receive an introductory phone call during which the health practitioner will explain their support role and schedule the weekly contact. Alternatively, participants will have the option to proceed without practitioner contact. In either case, participants will be prompted to consider the option of talking to someone at several points within the online intervention.

At the end of each module, printable summary pages of their inputs may be emailed to participants, their support people, and members of their Healing Circle as attachments according to participant preferences. With the participant’s permission, this summary may also be emailed to their allocated practitioner, if they have one. Participants will be sent an email or text to remind them to log in each week regardless of which modules have been completed. If all modules are completed early, participants may repeat modules. All online interactions will be monitored and inputs recorded but de-identified prior to analysis.

The online intervention has been developed so that a range of health practitioners may provide optional clinical support as an adjunct to the program. Health practitioners providing support will have received face-to-face training from the research team and a training manual with detailed instructions in the use of the online intervention and how it may be used as the basis for supportive conversations that consolidate the online intervention content. The manual contains examples of scripts to guide conversations. If issues arise in these conversations that fall outside the practitioners’ professional boundaries, they will have clear referral pathways available to them. Ongoing support for health practitioners will be provided throughout the trial by the research team and senior clinicians in each organization.

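### No prompted adverse-event question common to both arms is described, and scheduled practitioner calls belong to the intervention arm's support, so recorded harms may not be comparable between arms

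*Protocol article*

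**What the plan says.** **Capture of harms.** Safety and Security gives the rule. The trial management committee is to assess "Adverse events or unintended effects of the trial reported by participants or clinicians involved in the trial". The committee then passes events to the ethics committees and others as required. Emergency and researcher numbers are on the information sheet and at the end of the baseline and follow-up assessments, with no distinction by arm.

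**Practitioner contact, intervention arm.** Trial Design: "The intervention group will receive the We Can Do This online intervention with the option of telephone or face-to-face support provided by their local ACCHS". Implementation (text after the Figure 1 caption): "Participants will have the option of receiving health practitioner support via weekly phone calls from trained staff at the participating health service", starting with an introductory call. The support can be declined: "Alternatively, participants will have the option to proceed without practitioner contact".

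**Practitioner contact, control arm.** Trial Design: "Treatment as usual will involve referral to online harm minimization information and access to alcohol and other drug counseling at the participating health service". No scheduled calls are described for controls.

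**Contact common to both arms.** Trial Design: "The wait-list control group will undertake the same assessments as the intervention group and have access to treatment as usual". Data Collection and Management: "Data will be collected online at baseline, and at 1, 2, and 3 months postbaseline", with telephone follow-up after the online invitation.

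**Measures listed.** Primary Outcome and Secondary Outcomes name methamphetamine use days, help-seeking, readiness to change, Kessler 10 distress, poly-drug use, severity of dependence, days out of role, and usability and acceptability. None is an adverse-event item.

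**The concern.** When harms are recorded through reports and not through a question put to everyone, the count depends on how often someone is in a position to hear about an event. Here that opportunity differs by design. An intervention participant who accepts support speaks every week to a trained practitioner who can report to the committee. A control has no such scheduled contact, and neither does an intervention participant who declines support.

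The article itself names a plausible harm. Focus testing found that the emotive content of some films could be triggering, and this led the team to strengthen safety measures (Incorporation of Feedback From Focus Testing). The Introduction also reports stigma and shame as barriers to health services in this population, so contact that the participant must start may be a weak channel.

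Two things are at stake: whether events in participants without a practitioner reach the committee, and whether any later tabulation of harms by arm reflects the program or the intensity of contact.

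**Working it through.** The article states no adverse-event rate, capture rate or expected uptake of support, so there is no figure to reproduce. The check has two parts.

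**1. Which channels treat the arms alike?**

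- *Participant-started report using the displayed numbers:* open to both arms and not restricted by arm.
- *Practitioner report from scheduled calls:* intervention arm only, and only for those who accept.
- *Practitioner report from usual counseling:* open to controls at the same services, but not scheduled.
- *Health-service contact data:* described as contact arising from use of the program, so by its wording it does not cover controls before they get access.
- *Free text in the adherence questionnaire and interviews with users:* concern people who used the program.
- *Kessler 10, use days and the other scales at 1, 2 and 3 months:* both arms alike, but these are scores and counts. They record neither an event nor whether the participant links it to the program.

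No channel is at once scheduled, common to both arms and directed at events.

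**2. How far could recorded events differ if true risk is equal?**

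The only input from the document is 144 recruited per arm (Sample Size and Power), used for scale. All other inputs are assumptions:

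- true event risk p = 10% in both arms;
- capture probability c0 without calls and c1 with calls;
- uptake of calls u, which the article leaves open from 0 to 100%.

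Formulas:

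- True events per arm = 144 × 0.10 = 14.4
- Recorded, control = 14.4 × c0
- Recorded, intervention = 14.4 × [u × c1 + (1 − u) × c0]
- Apparent ratio = [u × c1 + (1 − u) × c0] / c0

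The true risk cancels from the ratio. Example with c0 = 30%, c1 = 60%, u = 50%: control 14.4 × 0.30 = 4.3; intervention 14.4 × (0.5 × 0.60 + 0.5 × 0.30) = 14.4 × 0.45 = 6.5; ratio 0.45 / 0.30 = 1.5.

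| Assumed c0 / c1 | Control recorded | Intervention recorded at u = 0, 25, 50, 100% | Apparent ratio at the same uptakes |
|---|---|---|---|
| 20% / 60% | 2.9 | 2.9, 4.3, 5.8, 8.6 | 1.0, 1.5, 2.0, 3.0 |
| 30% / 60% | 4.3 | 4.3, 5.4, 6.5, 8.6 | 1.0, 1.25, 1.5, 2.0 |
| 50% / 80% | 7.2 | 7.2, 8.3, 9.4, 11.5 | 1.0, 1.15, 1.3, 1.6 |
| 50% / 50% | 7.2 | 7.2, 7.2, 7.2, 7.2 | 1.0, 1.0, 1.0, 1.0 |

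In every row both arms record fewer than the 14.4 true events. The ratio is exactly 1.0 if nobody takes the calls or if calls do not raise capture.

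**The case against.** The strongest reply is that this is a condensed article. The wording on reports neither says that they must be spontaneous nor excludes prompted ones, and the procedure for eliciting events may well be in the full protocol. This stands in part. A reader might infer that events count only when someone volunteers them, but the text does not say so. What can be said is that the article states a reporting rule and lists its measures in some detail, and that no prompted item common to both arms appears in either place.

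A reader might also infer that harms would be over-counted in the intervention arm. The working contradicts that. More contact finds more of the true events, so that arm would be less under-counted than control and would not be counted above the truth.

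Third, no between-arm comparison of adverse events is planned. Statistical Analyses and End Points compares the primary and secondary outcomes, and adverse events are neither. The committee reviews reported events, and unequal capture matters less for case review than for comparing rates. This stands: a committee misled by a spurious risk ratio cannot be presented as a consequence of the plan. At these sample sizes the illustrated excess is also only a few events.

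Finally, both arms already give Kessler 10 scores and use days, which bear directly on being distressed or triggered, and controls can see counselors at the same services. This also stands as partial mitigation. It does not supply a record of events or of their attribution.

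**Conclusion.** The point holds as a risk of unequal and incomplete ascertainment, not as a demonstrated bias. The described route relies on reports from participants or trial practitioners, scheduled practitioner contact is part of one arm's optional support, and no listed measure asks everyone about adverse or unintended effects. Recorded events could therefore be less under-counted in the intervention arm than in controls, and events in anyone without a practitioner could be missed.

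The likely direction is more recorded events in the intervention arm. The size cannot be derived from the document. Under the assumed capture rates above, the ratio lies between 1.0 and 3.0, and its upper end needs both full uptake and a threefold gain in capture. The primary and secondary efficacy comparisons are unaffected. This is a worthwhile, inexpensive improvement and not an error in the stated analysis. If the full protocol already has a prompted item for both arms, one sentence in Safety and Security would settle it.

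**What to change.** Add one short, identically worded item on adverse or unintended effects to the existing 1-, 2- and 3-month assessments in both arms, online or by telephone for those followed up that way. It could ask about any event since the last assessment that was distressing or needed urgent care, and then whether the participant links it to the study.

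In Safety and Security, state that any summary of harms by arm uses these solicited reports, and that spontaneous participant or practitioner reports are listed separately. Keep the spontaneous route: the sample-size section expects up to 30% attrition, and the solicited item will not reach people who miss assessments.

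The cost is one or two questions on assessments that are already scheduled and reimbursed, plus a sentence or two of text. The downside is slightly longer assessments and more events for the committee to review.
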